## Methods and analysis

### Trial design and setting

This study represents a model of implementation to demonstrate the value of adopting a life-course approach and integrated care to maternal–child health. It is conceptualised as a single-arm trial, with a targeted intervention implemented in a group of women living with obesity who are trying to conceive within 1 year after recruitment. The longitudinal intervention will be performed from preconception, throughout pregnancy until 18 months postpartum in the KK Women’s and Children’s Hospital (KKH), Singapore. The protocol is written following the SPIRIT (Standard Protocol Items: Recommendations for Interventional Trials) guidelines. Written informed consent will be obtained from all participants at the recruitment.

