### Planned analyses

Continuous variables will be presented as means and SD, or medians and 25th–75th centiles, as appropriate. Categorical variables will be presented as numbers and percentages. The pregnancy rate will be determined by the number of women who became pregnant (defined as stated previously) divided by the total number of women who completed the 1-year follow-up during the preconception phase. The time to pregnancy (TTP) will be estimated by the number of menstrual cycles required to achieve pregnancy over 1 year of follow-up. We will use the discrete-time proportional hazards model, which analyses TTP as a discrete scale based on the number of menstrual cycles, to estimate the fecundability ratio (FR) and the 95% CI,^43 44^ accounting for left truncation and right censoring. For the other two coprimary outcomes, a linear mixed effects model will be used to examine changes in means between the baseline and follow-up metabolic markers and EPDS scores, with adjustment for baseline potential confounders (including partner’s characteristics) and duration of the intervention received. In addition to the pre–post comparison of outcomes stated above, differences in pregnancy and birth outcomes will also be compared with a similar observational cohort in Singapore called Singapore PREconception Study of long-Term maternal and child Outcomes (S-PRESTO),^45^ using multiple linear or logistic regression models, adjusting for potential confounders. These confounders, such as age, ethnicity and education, will be determined from literature review, directed acyclic graph and/or observed statistically significant associations with exposures and outcomes.

We will impute missing data using multiple imputation analyses by chained equations.^46^ The number of imputations will be determined based on a percentage of missing values,^47^ and the results of total imputations will be pooled using Rubin’s rule.^48^ To determine whether the imputation of the missing data may have affected the results, we will perform sensitivity analyses on participants with a complete set of data.

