### Sample size calculation

Based on the S-PRESTO study,^45^ which is an observational cohort recruited from preconception and followed up through postpartum periods, preconception overweight or obese women (BMI ≥25 kg/m^2^) had a 38% pregnancy rate, while those with normal weight (BMI 18.5–24.9) had 47% pregnancy rate. Among overweight and obese women, those with healthy metabolic profiles characterised by absence of the metabolic syndrome or insulin resistance had a 52% pregnancy rate. We anticipated that HELMS intervention will improve overweight or obese women’s pregnancy rate from 38% to 50% within 12 months of trying. Using a two-sided α level of 5% and a power of at least 90%, 400 participants are needed in the preconception phase, leading to 200 pregnancies. Considering a 20% drop-out rate, 500 participants are required for recruitment. We estimated that 15% of women will experience pregnancy loss and another 10% drop-out, leaving 150 dyad pairs to be followed.

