Despite the strong evidence base for adverse maternal and child outcomes in overweight and obese women, as well as the benefit of lifestyle interventions in the preconception and pregnancy phases, integrated HELMS interventions are novel and have not established unequivocal evidence of benefit. Thus, HELMS is conceptualised as a single-arm intervention trial in women living with overweight or obesity to obtain preliminary evidence of the efficacy of intervention. A subsequent larger pragmatic trial is envisaged to validate the efficacy of the intervention. The main limitations of this study design include the inability to distinguish between the effect of intervention, a placebo effect and the effect of natural history, including regression to the mean. Given the similarity in study design to the prospective observational cohort S-PRESTO, with similar time points of follow-up and biosampling, there is the potential for comparison with this historical cohort. HELMS is a single-centre study of the Asian population, involving only English-speaking participants, thus, the external validity may be limited to this population, and caution will need to be exercised in generalising results across different settings and populations. Finally, the interventions are tailored to the woman/mother, with only passive intervention for her partner. The environment of the woman plays an important role in her compliance to lifestyle interventions,^53^ which may undermine the impact of our programme. On the other hand, if the success of the HELMS interventions extends to that of her immediate family, we would also have limited insights with minimal measurements on the partner, to reduce the burden of involvement in the study.

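### The plan lets observed statistical significance choose the confounders for the S-PRESTO comparison; used alone, that screen drops true confounders and leaves their bias in the estimate

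*Protocol article*

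**What the plan says.** The article describes a trial without a concurrent control (Trial design and setting: "It is conceptualised as a single-arm trial"). Under Planned analyses, pregnancy and birth outcomes "will also be compared with a similar observational cohort in Singapore", namely S-PRESTO, "using multiple linear or logistic regression models, adjusting for potential confounders". The next sentence gives the rule for choosing those confounders. They are to come from literature review, a directed acyclic graph *and/or* "observed statistically significant associations with exposures and outcomes".

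Three variables are named, but only as examples: "These confounders, such as age, ethnicity and education". The article states no closed set and no order of precedence among the three sources. The Discussion returns to the comparison more tentatively: "there is the potential for comparison with this historical cohort".

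**The concern.** In this regression the exposure is cohort membership, HELMS or S-PRESTO. Screening a covariate for association with exposure is therefore a significance test of imbalance between two non-randomised groups. Whether it passes depends on sample size as well as on the size of the imbalance. A covariate that truly differs between cohorts and truly predicts the outcome can miss p<0.05 on either screen. It is then left out, and its bias remains in the estimate.

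Even where the screen only adds covariates to a set fixed on subject-matter grounds, the final model depends on the outcome data and can differ from one outcome to the next.

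This matters because pregnancy and birth outcomes have no baseline value: women who are pregnant at entry are excluded (Participants and recruitment). The pre–post comparison that serves the metabolic and EPDS outcomes is not available for them, and S-PRESTO is the only external comparator the article names.

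**Working it through.** The article gives no figure for this rule, so there is none to reproduce. The check asks how often the screen would miss a real confounder, and what that does to the comparison.

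**Inputs from the article (Sample size calculation).** 200 pregnancies, 15% pregnancy loss and a further 10% drop-out. So 200 × 0.85 = 170 pregnancies remain after loss, and 200 × 0.75 = 150 dyads.

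**Assumed inputs.** The usable size of S-PRESTO and the number, strength and direction of the confounders are not given. The 5% two-sided level is taken from the sample size calculation and used for both the screens and the final test.

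**Step 1: chance that a real imbalance is detected.** For a standardised covariate with a true difference of 0.2 SD and n per cohort, SE = √(2/n) and the chance of p<0.05 is about Φ(0.2/SE − 1.96).
- n = 170: SE = 0.1085, 0.2/SE = 1.844, Φ(−0.116) ≈ 45%.
- n = 150: SE = 0.1155, 0.2/SE = 1.732, Φ(−0.228) ≈ 41%.

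More than half of such imbalances are missed before the outcome screen is applied.

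**Step 2: bias with no adjustment.** With k confounders, shift δ and outcome slope β, all of one sign, bias = kδβ.
- k = 8, β = 0.12: 8 × 0.2 × 0.12 = 0.192 SD.
- k = 5, β = 0.15: 5 × 0.2 × 0.15 = 0.150 SD.
- k = 3, β = 0.15: 3 × 0.2 × 0.15 = 0.090 SD.

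**Step 3: simulation.** Linear outcome, no true effect, 170 per cohort, 4,000 datasets per scenario. A covariate is kept only if p<0.05 with both cohort and outcome. Ranges are over repeated runs.

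| Confounders, same direction | Bias with screen alone | Type I error, screen alone | Type I error, all adjusted |
|---|---|---|---|
| 8 | about 0.09 SD | 11.9–12.1% | 5.0–5.3% |
| 5 | about 0.06 SD | 7.0–8.2% | 4.5–5.1% |
| 3 | about 0.035 SD | 6.0–6.8% | 5.3–5.8% |

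Full adjustment gave bias of about zero. With eight confounders each was kept only 29% of the time, and roughly half of the unadjusted bias survived (0.088/0.192 = 46%). The Monte Carlo standard error near 8% is √(0.08 × 0.92/4000) = 0.4 points, so the three-confounder excess is barely distinguishable from noise.

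**Step 4: less adverse assumptions, same sizes.**
- Confounder signs alternating, screen alone: type I error between 4% and 5% with eight, and about 5% with five or three. Bias is at most 0.013 SD.
- Same signs, three confounders always kept and the rest screened: about 8% with eight, 5.5% with five, 5.1% with three.
- Same signs, six of eight always kept: 6.0%, bias 0.02 SD.

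**Step 5: other sizes.** 150 HELMS women against 150 or 350 comparators, four or eight same-direction confounders, shifts and slopes of 0.1 to 0.3, 1,000 runs each. Screening alone kept true confounders 6% to 87% of the time, gave bias of 0.02 to 0.12 SD and 95% interval coverage of 86% to 95%. The fixed full set gave bias of about zero and coverage of 94–95%. In the mildest case (four confounders at 0.1, 150 per cohort) coverage was 94.8% either way.

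Most of the lost coverage comes from bias. The largest shortfall of the model standard error against the empirical SD was 0.104 against 0.110, about 5%. In that scenario full adjustment also fell short (0.102 against 0.106, about 4%).

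**The case against.** The strongest reply is that the article lists literature review and a directed acyclic graph first and names age, ethnicity and education. On an inclusive reading, significance only supplements that set, and no confounder named by the literature or graph is dropped. This stands as a plausible reading, and Step 4 shows that the inflation is then small unless many same-direction confounders are missing from both sources. But the sentence does not say so, and on that reading the covariates still depend on the outcome data.

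A second reply is that the covariate list belongs in the analysis plan, which is not shown. That is fair for the list. The significance criterion, however, is a rule the article states, and a plan that follows the article could apply it.

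Third, the comparison is additional to the pre–post analyses, the trial is described as seeking preliminary evidence, and the limits of a single arm are conceded. This stands and limits the importance of the point.

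Four stronger inferences are tempting and are not supported:
- That the significance screen will be used alone. The text permits this but does not require it.
- That variables changed by the intervention, such as later weight, will be adjusted away. Nothing in the article proposes this. The named examples are not of that kind, and a graph serves to exclude such variables.
- That the rule favours false claims of benefit. Residual confounding from a non-randomised cohort can run either way and can also hide a benefit.
- That the intervals are materially too narrow because they ignore selection. Step 5 shows this is the minor part.

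**Conclusion.** The concern holds in a limited form. The stated rule allows an observed-significance screen to choose the confounders, alone or as a supplement, for the only external contrast available for pregnancy and birth outcomes.

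The 12% type I error is a worst case: eight confounders, all biasing the same way, screen alone. The excess shrinks with fewer confounders, all but disappears if their directions oppose, and is 0 to 3 points if three are always kept. All these sizes rest on assumed confounder number, strength and direction and on an assumed comparator size. They were worked for a linear outcome only; the logistic models were not simulated. The point should be corrected because the change is small and removes an avoidable source of bias. It does not invalidate the trial's other analyses.

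**What to change.** In Planned analyses, delete observed statistical significance as a route for choosing confounders, or confine it to a sensitivity analysis labelled as such. Before the S-PRESTO comparison is run, fix one covariate set from the directed acyclic graph and literature. Limit it to variables measured at or before baseline in both cohorts, and keep the whole set in every model whatever the p-values.

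The article already names the graph and literature as sources, so this changes about one sentence and needs no new data. The cost is a slight loss of precision if some retained covariates turn out not to matter.

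### The one named check on imputation, a complete-case analysis, cannot detect drop-out that depends on the unseen outcome, and it adds nothing for the pregnancy rate, which is already a completer figure

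*Protocol article*

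**What the plan says.** All references are to the protocol article.

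- **Planned analyses, missing data.** "We will impute missing data using multiple imputation analyses by chained equations", pooled by Rubin's rule. One sensitivity analysis follows: "we will perform sensitivity analyses on participants with a complete set of data". Its purpose, as the article gives it, is this: "To determine whether the imputation of the missing data may have affected the results". No other missing-data sensitivity analysis is named.
- **Planned analyses, pregnancy rate.** Pregnancies are divided by the number of women with a complete year of preconception follow-up. Separately, a discrete-time model of time to pregnancy allows for right censoring. Metabolic markers and Edinburgh Postnatal Depression Scale (EPDS) scores go into linear mixed models.
- **Sample size calculation.** The target is a rise in "pregnancy rate from 38% to 50% within 12 months of trying". It states that "400 participants are needed in the preconception phase, leading to 200 pregnancies". Then: "Considering a 20% drop-out rate, 500 participants are required for recruitment". For the later phases it expects "15% of women will experience pregnancy loss and another 10% drop-out, leaving 150 dyad pairs to be followed".
- **Trial design and setting; Participants and recruitment.** There is a single arm. Women who do not conceive have an exit visit at 12 months. Women who cannot follow the protocol, or who want to stop, are withdrawn.

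**The concern.** Imputation by chained equations, as normally run, assumes that women with missing values resemble women with the same recorded data who stayed. Complete-case analysis generally assumes at least as much. If a woman's chance of leaving depends on the outcome that was never recorded, beyond what her recorded data explain, both analyses are wrong in the same direction. Their agreement is then no evidence that the result is sound.

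Such drop-out is plausible here. A woman who conceives early has her outcome recorded early, while a woman who does not must stay to month 12 to be counted, so non-conceivers have longer in which to leave. With one arm, no concurrent group shares the loss and lets the bias cancel.

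For the pregnancy rate the difficulty goes further. Because the stated denominator is completers, drop-outs are outside the estimate, there is no missing outcome in it to impute, and the complete-case check coincides with the main analysis. The article does not say how the imputation statement relates to this denominator. What is at stake is how much of the planned 12-point improvement survives once the 100 women expected to drop out are considered.

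**Working it through.** **Inputs (Sample size calculation):** historical rate 38%, target 50%, 400 completers, 200 pregnancies, 20% drop-out, 500 recruited.

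**1. The plan's own figures.**
- Recruitment: 400 / (1 − 0.20) = 500, as stated, so 100 women are expected without a 1-year outcome.
- Completer rate: 200 / 400 = 50%.
- Dyads: 200 × (1 − 0.25) = 150, as stated.

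**2. Rate over all 500 women.** If drop-outs conceive at rate r, the overall rate is p = (200 + 100r) / 500. The test against a fixed 38% is z = (p − 0.38) / √(0.38 × 0.62 / 500), with standard error 0.0217.

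| r in drop-outs | p over 500 | gain over 38% | z |
|---|---|---|---|
| 50% | 50.0% | 12.0 points | 5.53 |
| 38% | 47.6% | 9.6 points | 4.42 |
| 25% | 45.0% | 7.0 points | 3.22 |
| 10% | 42.0% | 4.0 points | 1.84 |
| 0% | 40.0% | 2.0 points | 0.92 |
| 100% | 60.0% | 22.0 points | 10.13 |

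**3. Tipping point against a fixed 38%.** The critical rate is 0.38 + 1.96 × 0.0217 = 0.4225, so r = (0.4225 × 500 − 200) / 100 ≈ 0.11. This treats the 500 outcomes as known; imputation uncertainty would lower z somewhat.

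**4. Tipping point against a sampled historical cohort.** The article does not give the number of overweight and obese women behind the 38%, so a size m is assumed. With a pooled two-sample z-test of p in 500 against 38% in m, z reaches 1.96 at r of about 31% (m = 200), 25% (m = 300), 22% (m = 400) and 20% (m = 500). For m = 400, z is 1.82 at r = 20% and 2.12 at r = 25%.

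**5. Can the named check see this?** Take a programme with no effect: 38% of all 500 conceive and 80% are retained overall. Assume 95% of pregnant women are retained. Then:
- Retention of the others is (0.80 − 0.38 × 0.95) / 0.62 = 70.8%.
- The completer rate is 0.38 × 0.95 / 0.80 = 45.1%.
- For 400 women against a fixed 38%, z = (0.45125 − 0.38) / √(0.38 × 0.62 / 400) = 2.94.

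A simulation of this case (400 runs of 500 women, one assumed baseline covariate, 20 imputations) gave a true rate of 38.3%, a complete-case rate of 45.5% and an imputed rate of 45.2%. The two analyses agree to 0.3 points and share a bias of about 7 points.

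**6. Where the 20% applies.** It is preconception drop-out. The principal time point for metabolic health and EPDS is 18 months after delivery, where 150 dyads are expected from 500 recruits (30%). Part of that reduction is by design, since women who do not conceive leave at 12 months. The table above therefore says nothing about those two outcomes.

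**The case against.** **The check does what it claims.** The article gives the complete-case analysis a narrow purpose, whether imputation changed the results, and it serves that purpose. Nowhere is it presented as a test of outcome-dependent drop-out. This stands, and it is why the fix keeps the analysis.

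**More may be planned elsewhere.** Tipping-point analyses are often left to a statistical analysis plan, which is not shown. A reader might infer that no other sensitivity analysis exists; the article cannot support that. What can be assessed is the choice it does state: it names its sensitivity analysis and fixes its pregnancy denominator, and neither addresses this kind of loss.

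**The two analyses need not agree.** A reader might infer that any drop-out related to conception, mood or weight escapes the check. That is too strong. Weight is logged weekly, and questionnaires and measurements are repeated. If leaving follows those recorded values and the imputation model uses them, imputation can correct the bias where complete-case analysis does not, and the two would differ. Only dependence on unrecorded values stays hidden.

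**The time-to-pregnancy model uses partial follow-up.** True: women who leave early contribute cycles until censoring. But that model assumes censoring is uninformative given its covariates, and it does not produce the headline pregnancy rate.

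**The low bound is extreme and its comparator uncertain.** Also fair. The range runs upward to 60% as well as down to 40%, and at 25% or 38% conception in drop-outs the result remains significant against a fixed 38%. The article does not say how the denominator of the historical 38% was formed, so comparing it with an all-enrolled rate may not be like for like.

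**The study seeks preliminary evidence.** The Discussion says so and admits the limits of a single arm. That lowers the stakes but does not make the completer rate more robust.

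**Conclusion.** The concern holds in a limited form. The named complete-case analysis can show whether imputing mattered, but it cannot detect drop-out that depends on the unobserved outcome. For the pregnancy rate, as defined on completers, it adds nothing to the main estimate.

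At the planned figures, the 50% completer rate corresponds to 47.6%, 45.0% or 40.0% over all 500 women if drop-outs conceive at 38%, 25% or 0%, and to 60% if all do. Against a fixed 38%, the conclusion changes only when drop-outs conceive at below about 11%. Against a sampled historical cohort of an assumed 200 to 500 women, it changes at about 31% down to 20%.

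Two stronger readings are not supported. One is that 10 of the 12 target points are likely to vanish: that is the bound with no drop-out pregnant, not an expectation. The other is that 20% drop-out threatens all three primary outcomes alike: it belongs to the preconception phase, and the article gives no basis for sizing the bias in the 18-month outcomes.

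The figures assume exactly the planned 400 completers and 200 pregnancies. The retention pattern in the no-effect example is assumed for illustration. This should be addressed before analysis; it does not stand in the way of the trial.

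**What to change.** - **Pregnancy rate.** Report it over all eligible enrolled women with missing outcomes imputed, and state how this relates to the completer rate now defined. Keep the completer rate and the complete-case analysis as descriptive results.
- **Delta-adjusted (tipping-point) analysis.** On the same imputed data, lower the odds of pregnancy in drop-outs by prespecified steps and report the step at which the conclusion changes. Add the bound that counts every drop-out as not pregnant.
- **EPDS and metabolic markers.** Run the same kind of analysis, worsening imputed values by fixed steps, only among women due for the visit, so that women who left by design after not conceiving are not treated as missing.
- **Wording.** Say that the complete-case comparison shows the influence of imputation and does not test for outcome-dependent drop-out.

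The cost is a few additional runs of imputation code already planned, with no extra participants or visits. The downside is that the reported range may look less favourable than the completer figure alone.

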### Sample size calculation

Based on the S-PRESTO study,^45^ which is an observational cohort recruited from preconception and followed up through postpartum periods, preconception overweight or obese women (BMI ≥25 kg/m^2^) had a 38% pregnancy rate, while those with normal weight (BMI 18.5–24.9) had 47% pregnancy rate. Among overweight and obese women, those with healthy metabolic profiles characterised by absence of the metabolic syndrome or insulin resistance had a 52% pregnancy rate. We anticipated that HELMS intervention will improve overweight or obese women’s pregnancy rate from 38% to 50% within 12 months of trying. Using a two-sided α level of 5% and a power of at least 90%, 400 participants are needed in the preconception phase, leading to 200 pregnancies. Considering a 20% drop-out rate, 500 participants are required for recruitment. We estimated that 15% of women will experience pregnancy loss and another 10% drop-out, leaving 150 dyad pairs to be followed.

